### *Aim 2*: Validation of mobile application-based behavioral metrics as measures of inhibitory control

In order to robustly measure inhibitory control, we will employ a framework through which a latent factor of inhibitory control is computationally derived from measurements of motor inhibition across four canonical inhibitory control laboratory-based tasks described above [59]. This latent factor will be computed using confirmatory factor analysis with a measure of inhibitory control from each of the four tasks loading onto a single latent factor. By leveraging latent variable analysis across a range of tasks that differ in their behavioral goals, response modality, and context, we can quantify a relatively pure measure of inhibitory control that is immune from task-specific impurities and thus increase statistical power. Next, we will extract individual-level inhibitory control latent factor scores for each participant to examine associations with mobile application-based measures of inhibitory control. We will conduct a multiple regression analysis with CALM-IT d’ as a predictor of inhibitory control latent factor scores, with age, sex, order of task completion (e.g., CALM-IT or laboratory testing administered first), and IQ entered as covariates.

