## Methods

### Participants

Youth aged 8–18 years old will be recruited from the community to participate in research at the National Institute of Mental Health (NIMH). Participants will be recruited as part of a larger protocol that aims to specifically recruit youth with a primary diagnosis of an Anxiety Disorder, Disruptive Mood Dysregulation Disorder (DMDD), ADHD, and youth with no psychiatric diagnosis. Past work within this sample has found that recruiting samples characterized by these clinical diagnoses has resulted in the full range of irritability, anxiety, and ADHD symptoms [51,59–62]. All diagnoses will be assessed by a Board-Certified psychiatrist or licensed psychologist using the Schedule for Affective Disorders and Schizophrenia for School-Age Children-Present and Lifetime version (KSADS-PL; [63]). Exclusionary criteria for participation will include an IQ<70, diagnosis of autism spectrum disorder, past and/or current post-traumatic stress disorder, schizophrenia, or depression, or neurological disorder.

Prior to participation, parents will provide written informed consent and youth will provide written assent. Participants will complete up to three different testing sessions. Administration of CALM-IT will occur outside of the laboratory setting. Families will be sent instructions on how to download CALM-IT onto their mobile device. As such, CALM-IT testing sessions will be completed within a community setting (e.g. at home) at whatever time is most convenient for the family. Parents will be instructed that CALM-IT should be played only by the child with no assistance. Adherence to this procedure will be assessed in a follow up interview. Families will also have the option of coming in for in-laboratory testing where children will complete four canonical inhibitory control tasks (detailed below). Families will receive monetary compensation for completion of CALM-IT. All study procedures have been approved by the NIMH Institutional Review Board.

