To investigate the feasibility of CALM-IT (***Aim 1a***), we will recruit 200 youth. For investigation of the stability of CALM-IT (***Aim 1b***), we will invite 75 youth out of the overall sample of 200 to play CALM-IT twice. For validation of mobile application-based behaviors of inhibitory control (***Aim 2***), we will invite 100 youth out of the overall sample of 200 to complete a battery of in-laboratory inhibitory control paradigms. We evaluated each of these proposed sample sizes using the pwr package in R to determine the size of the effect that the sample would allow us to detect using a significance level of 0.05 and a power level of 0.80 [64]. For the feasibility of CALM-IT (***Aim 1a***), our proposed sample size is sufficient to detect effects of *r*≥0.20. For the stability of CALM-IT (***Aim 1b***), our proposed sample size is sufficient to detect effects of *r*≥0.32. Finally, for the validation of application-based behaviors of inhibitory control (***Aim 2***), the proposed sample size is sufficient to detect effects of *r*≥0.28. Thus all proposed samples would allow us sufficient power to detect small to medium effect sizes that are similar to those found within comparable samples [7,47,65,66].

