#### Stability of mobile application-based behaviors

In the subset of participants who completed the mobile application twice, one week apart from another, the temporal stability of mobile application behaviors will be assessed using test-retest reliability. Specifically, we will examine test-retest reliability through examination of correlation between time-one with time-two measures of percentage of targets hit, percentage of stars hit, and d’. Consistency will also be reported using the intraclass correlation coefficient (ICC). In contrast to the Pearson’s correlation coefficient, ICC captures not only the degree of correlation, but also the agreement across measurements [74,75]. Because we are investigating test-retest reliability, or the stability across measurement, we will use ICC(3,1) which is a two-way mixed effects assessment of consistency within a single measurement. An ICC value of less than 0.40 would indicate poor consistency, an ICC value of 0.40–0.70 would indicate moderate consistency, an ICC value of 0.70–0.90 would indicate good consistency, and an ICC value greater than 0.90 would indicate excellent consistency.

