### *Aim 3*: Identify clinical correlates of mobile application-based behavioral metrics

First, raw bivariate correlations between raw total scores on the five symptom measurements and CALM-IT d’ will be examined. Next, associations with shared vs. unique variances of anxiety, irritability, and ADHD symptoms will be examined using multiple regression analyses. All four latent factor scores from the bifactor model will be entered as concurrent predictors of CALM-IT d’. For all models, any demographic variable that varies as a function of either symptoms and/or CALM-IT d’ will be included as a covariate (i.e., age, sex, and IQ). Finally, secondary analyses will be run examining bivariate correlations between measures of hyperactive-impulsivity, inattentiveness, and depression.

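### Aim 3 omits the lab-first order term that Aim 2 includes, although CALM-IT d' is the outcome in Aim 3

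*Protocol article*

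**What the plan says.** **Sequence.** Under Participants, the article says "Participants will complete up to three different testing sessions". CALM-IT is played at home "at whatever time is most convenient for the family", and the laboratory visit is optional: "Families will also have the option of coming in for in-laboratory testing where children will complete four canonical inhibitory control tasks". No order is fixed there.

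**Samples.** The article states "we will recruit 200 youth". From these, 75 are invited to play twice and 100 to attend the laboratory. The overlap of the two subsets is not stated.

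**Aim 2.** The laboratory latent factor is regressed on CALM-IT d', with age and sex as well as "order of task completion (e.g., CALM-IT or laboratory testing administered first), and IQ entered as covariates". Laboratory-first is thus an expected sequence.

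**Aim 3.** CALM-IT d' is the outcome and the four bifactor scores are the predictors. The covariate rule is that "any demographic variable that varies as a function of either symptoms and/or CALM-IT d’ will be included as a covariate (i.e., age, sex, and IQ". Order of testing is not a demographic variable and does not qualify.

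**Aim 1b.** "In the subset of participants who completed the mobile application twice, one week apart from another", stability is assessed by an unadjusted correlation and ICC(3,1).

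**The concern.** The same d' appears in all three aims, but order of testing is handled in only one. The section on the CALM-IT mobile application models galaxies 6-10 on the stop-signal paradigm. The laboratory battery includes that paradigm, with 330 go-trials and 110 stop-trials. A child who has just done 440 such trials may play differently from one who has not.

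In Aim 3, a shift in some children's d' that is unrelated to symptoms is extra noise. If families who come to the laboratory first differ in symptoms, which is possible because attendance is optional, part of the shift would be reported as a symptom association, or would mask a real one.

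In Aim 1b, the retest correlation could move for a reason unrelated to the app, but only if some retest children are exposed and others are not.

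**Working it through.** **1. The plan's own figure.** The article gives a detectable r of 0.20 for 200 children at significance level 0.05 and power 0.80. The standard power formula for a correlation (t critical value, Fisher z with its small bias term, two-sided) gives 0.197, and power 0.814 at r = 0.20. The figure reproduces. Aim 3 has no sample size of its own, so 200 is assumed here.

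**2. Inputs the documents do not give.** These are assumptions:
- s, the shift in d' after laboratory exposure: 0.2, 0.5 or 0.8 SD.
- p, the share of all children tested laboratory-first: 0.25, that is 50 of 200, or half of the 100 laboratory children. The ceiling is 100/200 = 0.50.
- φ, the correlation of laboratory-first with symptoms: 0.2. With φ = 0 there is no bias.

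**3. Aim 3, noise only (φ = 0).** Let v = p(1 − p)s². A true r becomes r/√(1 + v). For p = 0.25, p(1 − p) = 0.1875.

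| s | v | r = 0.20 becomes | power (from 0.814) |
|---|---|---|---|
| 0.2 | 0.0075 | 0.199 | 0.811 |
| 0.5 | 0.0469 | 0.196 | 0.796 |
| 0.8 | 0.1200 | 0.189 | 0.768 |

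**4. Aim 3, bias (φ = 0.2).** With no true association, spurious r = φ·s·√(p(1 − p))/√(1 + v). For s = 0.5: 0.2 × 0.5 × 0.433/1.023 = 0.042. The type I error is the two-sided rejection rate at n = 200 for that r.

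| s | spurious r | type I error |
|---|---|---|
| 0.2 | 0.017 | 0.057 |
| 0.5 | 0.042 | 0.091 |
| 0.8 | 0.065 | 0.152 |

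At s = 0.5, changing φ to 0.1 or 0.3 gives a type I error of 0.060 or 0.145. At the ceiling p = 0.50 with φ = 0.2, the spurious r is 0.020, 0.049 and 0.074. These are bivariate calculations; the regression on four factor scores will differ somewhat.

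**5. Aim 1b.** The overlap of the 75 and the 100 can be 0 to 75 children; 75 × 100/200 = 37.5 is expected if the subsets are drawn independently. Take a true stability ρ = 0.70 for illustration, with p now the exposed share of retest children. Exposure between plays gives ICC(3,1) = ρ/(1 + v/2). Exposure before both plays gives (ρ + v)/(1 + v).

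| p | s | between plays | before both plays |
|---|---|---|---|
| 0.25 | 0.2 | 0.697 | 0.702 |
| 0.25 | 0.5 | 0.684 | 0.713 |
| 0.50 | 0.2 | 0.697 | 0.703 |
| 0.50 | 0.5 | 0.679 | 0.718 |
| 0.50 | 0.8 | 0.648 | 0.741 |

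A simulation of the case p = 0.50, s = 0.5, between plays, gave 0.678. With independent subsets, p = 0.50 needs practically every overlapping child to visit the laboratory within the one retest week. If a quarter of them do (p = 0.125), a 0.5 SD shift gives 0.70/(1 + 0.0273/2) = 0.691.

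**The case against.** **Carry-over is assumed.** The laboratory stop-signal task uses key presses, an auditory cue and a delay that tracks performance. CALM-IT uses swiping, a visual change and a random delay, and only galaxies 6-10 resemble that task. This stands: every size above is conditional.

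**The Aim 2 order term does not show that the authors expect d' to shift.** A reader might infer that it does. But the Aim 2 outcome is the laboratory factor, so the term may equally reflect concern that playing CALM-IT affects laboratory scores. What the term does show is that both orders will occur and that order is needed as a variable.

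**Nothing puts a laboratory visit between plays.** It is merely not excluded, and an article may leave visit scheduling to the larger protocol it mentions. This stands, and it makes the Aim 1b part a suggestion only.

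**Two stronger readings fail.**
- One might say the order covariate has only two levels and cannot represent play, laboratory, play. The article introduces the two orders as an example and does not fix the coding.
- One might say exposure pushes stability across the good/moderate cut at 0.70. That follows only from placing the true value on the cut. With s = 0.8 and p = 0.50, a true 0.80 becomes 0.80/1.08 = 0.74, and a true 0.60 becomes 0.56; neither changes category. At n = 75 the 95% interval around 0.70 is about 0.56 to 0.80, far wider than the shift.

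**Requiring all plays before the laboratory is not clearly better.** Order would become constant in Aim 2, and retest children would reach the laboratory after two plays while others had one. This stands too.

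**Conclusion.** The Aim 3 point holds. The article expects some children to be tested in the laboratory first and adjusts for order in Aim 2, yet its Aim 3 covariate rule leaves order out where d' is the outcome. This is a choice the article states, not a detail lost in condensing. With φ = 0 the cost is slight noise: power 0.768 to 0.811 instead of 0.814 under the assumed shifts. With φ = 0.2 and 25% laboratory-first, the spurious r is about 0.02 to 0.065 and the type I error about 0.06 to 0.15. Neither the shift nor φ can be read from the documents.

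The documents do not support saying that the Aim 1b stability estimate is compromised. For shifts up to 0.5 SD the ICC moves by about 0.02 or less, down if exposure falls between plays and up if it precedes both. A shift shared by all children leaves r and ICC(3,1) unchanged.

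**What to change.** **Aim 3.** Add a covariate for laboratory battery completed before the first play (yes/no) to the regressions. It is defined for all 200 children, because those who never attend the laboratory are coded no. Report the corresponding partial correlations beside the raw bivariate ones. The cost is one degree of freedom: with four factor scores and all three demographic covariates, the residual degrees of freedom fall from 200 − 8 = 192 to 191. The information is already needed for Aim 2. The term removes an average shift, not differences between children in how much they carry over.

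**Aim 1b.** Where possible, schedule the laboratory visit outside the retest week. Report r and ICC(3,1) again without children who had a laboratory visit between plays, as a sensitivity analysis. Keep all retest children in the primary estimate: excluding every overlapping child could leave about 75 − 37 = 38, and the detectable r would rise from 0.32 to about 0.44.

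No fixed sequence of plays before laboratory testing is needed.

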### *Aim 3*: Identify clinical correlates of mobile application-based behavioral metrics

First, raw bivariate correlations between raw total scores on the five symptom measurements and CALM-IT d’ will be examined. Next, associations with shared vs. unique variances of anxiety, irritability, and ADHD symptoms will be examined using multiple regression analyses. All four latent factor scores from the bifactor model will be entered as concurrent predictors of CALM-IT d’. For all models, any demographic variable that varies as a function of either symptoms and/or CALM-IT d’ will be included as a covariate (i.e., age, sex, and IQ). Finally, secondary analyses will be run examining bivariate correlations between measures of hyperactive-impulsivity, inattentiveness, and depression.

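### Aim 3's secondary correlations, and apparently its youth-report ones, are unadjusted over ages 8–18 with no adjusted counterpart, so they can partly reflect age

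*Protocol article*

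**What the plan says.** The Aim 3 section of the analytic plan has three steps.

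1. **First step.** "First, raw bivariate correlations between raw total scores on the five symptom measurements and CALM-IT d’ will be examined". No covariates are attached. The ADHD section under Symptom measures makes the ADHD total a raw score.
2. **Regressions.** The four bifactor scores (one general, three symptom-specific) enter together as predictors of d'. For these models "any demographic variable that varies as a function of either symptoms and/or CALM-IT d’ will be included as a covariate", followed by a parenthesis naming age, sex and IQ.
3. **Secondary step.** "secondary analyses will be run examining bivariate correlations between measures of hyperactive-impulsivity, inattentiveness, and depression". No covariates are attached, and the sentence does not say what these measures are correlated with.

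Three other places bear on the point. Under Participants, "Youth aged 8–18 years old will be recruited from the community". The bifactor section builds its factors from parent-report irritability items, parent-report anxiety subscales and six ADHD items, so youth-report scores do not enter. Aim 2 fixes its adjustment in advance, "with age, sex, order of task completion (e.g., CALM-IT or laboratory testing administered first), and IQ entered as covariates".

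**The concern.** Age is a plausible common cause over a ten-year developmental span. Performance on an inhibition task may change with age, and so may symptom scores. A raw correlation between the two then contains a part due to age alone. The plan itself treats age as a covariate in Aim 2 and in the Aim 3 regressions, but a bivariate correlation has no place for one.

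For the parent-report irritability, anxiety and ADHD scores this matters less, because those domains reappear in the adjusted regressions. Hyperactive-impulsivity, inattentiveness and depression do not reappear as measures in their own right. Neither do youth-report irritability and anxiety, if they are among the five first-step measurements. For these the unadjusted coefficient is the only planned result, and it would be read as a clinical correlate of the app measure.

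**Working it through.** **Inputs from the protocol.** Ages 8–18. Overall sample: "we will recruit 200 youth". Aim 3 has no sample size of its own, so N = 200 with complete data is assumed. Error and power: "using a significance level of 0.05 and a power level of 0.80", taken as two-sided.

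**Inputs assumed.** The documents give no age–d' or age–symptom correlation. The working range is 0.2–0.4 in size for age–d' and 0.2–0.3 for age–symptom. Wider values are shown for context.

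**Step 1: the plan's own figure.** For N = 200 the plan states "our proposed sample size is sufficient to detect effects of *r*≥0.20" (given for Aim 1a). By Fisher's z, r = tanh[(1.960 + 0.842)/√197] = tanh(0.1996) = 0.197. The formula used by the pwr package also gives 0.197, with power 0.814 at r = 0.20. The figure reproduces.

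**Step 2: size of the artefact.** With a = corr(age, d'), b = corr(age, symptom) and no association given age, the raw correlation is a × b. At N = 200 the two-sided critical value is |r| = √[1.972²/(1.972² + 198)] = 0.139. The table gives the false-positive rate from 20,000 simulated trials per row (age uniform on 8–18, linear age effect). The last column assumes that the regression rule is applied as p < 0.05 for age against either variable.

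| a | b | spurious \|r\| | unadjusted | age always in | rule in the regressions |
|---|---|---|---|---|---|
| 0.1 | 0.1 | 0.01 | 5.3% | 5.1% | 5.1% |
| 0.2 | 0.2 | 0.04 | 8.5% | 5.0% | 5.0% |
| 0.3 | 0.2 | 0.06 | 13.4% | 5.0% | 5.0% |
| 0.3 | 0.3 | 0.09 | 24.2% | 4.8% | 4.8% |
| 0.4 | 0.3 | 0.12 | 39.2% | 4.9% | 4.9% |
| 0.5 | 0.4 | 0.20 | 82.2% | 5.0% | 5.0% |

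The power formula agrees: 8.7% at |r| = 0.04, 13.5% at 0.06 and 39.6% at 0.12. The last row lies outside the working range. There the artefact equals the effect that the sample is sized to detect.

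**Step 3: why adjustment removes it.** The partial correlation is (r − ab)/√[(1 − a²)(1 − b²)]. With r = ab the numerator is zero.

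**Step 4: direction.** The artefact has the sign of a × b. If d' rises and a symptom falls with age, it is negative, which looks like an inhibition deficit. If both rise, it can mask one. Take a true partial correlation of −0.20 with a = b = +0.3. The raw value is −0.20 × 0.91 + 0.09 = −0.092, below the critical 0.139. The raw test then rejects about 25% of the time, against about 81% for the partial correlation.

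**Step 5: the regression rule.** A confounder must be related to both variables, while the rule admits a variable related to either. In the simulation age enters in 97% of trials at 0.2/0.2 and in over 99% at 0.3/0.2. At 0.1/0.1 it enters in only 50%, but the spurious r is then 0.01. Over all scenarios run, error was 4.6–5.1% under the rule and 4.7–5.1% with age fixed.

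**The case against.** The first-step correlations are openly called raw and precede the adjusted regressions, which carry Aim 3's question of shared versus unique variance. That stands for parent-report irritability, anxiety and ADHD, where the matter is mainly one of presentation. It does not cover measures that never reach a regression.

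The size rests on assumed age correlations. Recruitment is by diagnostic group, so the age–symptom relation in this sample is unknown, and at 0.1/0.1 the inflation is negligible. This also stands. The figures show what could happen, not what will.

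Depression and the two ADHD components are labelled secondary, and the missing d' in that sentence is probably an editorial slip, since the aim makes the other variable clear. Both are fair and limit the weight of the point. The protocol also does not say whether the ADHD subscales are raw or normed, so the objection to them is the lack of adjustment, not raw scoring.

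A reader might infer something stronger: that choosing covariates from the data leaves the Aim 3 regressions open to age artefact, or makes their coefficients non-comparable. The documents do not support this. The rule names age, sex and IQ, and step 5 shows that for age it performs like fixed adjustment. All four factor scores sit in one regression with one covariate set. What remains is that the rule states no threshold and its parenthesis can be read as a fixed list or as a list of candidates.

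**Conclusion.** The point holds for the unadjusted correlations only. It is strongest for hyperactive-impulsivity, inattentiveness and depression, which have no adjusted counterpart. It extends to youth-report irritability and anxiety on the inference that the five first-step measurements are the parent and youth versions of those two scales plus the ADHD total; the protocol does not list them. Within the working range the spurious |r| is 0.04–0.12 and the false-positive rate about 8–39%, against 5% with adjustment, in either direction. This assumes N = 200 with complete data, a linear age effect and a two-sided 5% test; sex and IQ were not simulated. It is a modest fault in supporting analyses, worth correcting because the remedy is nearly free.

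**What to change.** - In the first-step and secondary analyses, report the partial correlation of each symptom score with CALM-IT d', adjusted for age, sex and IQ. Keep the raw correlations beside them as descriptive.
- Name CALM-IT d' as the other variable in the secondary sentence.
- State that the parenthesis naming age, sex and IQ is a fixed covariate list, matching those three in Aim 2. This is for clarity and consistency, not to correct bias.

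The cost is wording plus 3 degrees of freedom out of about 200. By the power formula, power to detect r = 0.20 goes from 0.814 to 0.808. All three covariates are already in the plan, so no new data are needed.
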